### Statistical analysis and sample size

#### Summary of baseline data and flow of patients

We will perform an intention-to-treat analysis. The primary outcome (i.e. responder / non-responder status) will be analysed via χ^2^ test with α = 0.05. The proportion of responders in each arm, the difference thereof, and the 95% confidence interval for the difference in proportions will be reported.

Additional analyses may be performed to explore the consistency of the effect across subgroups, for instance defined by the degree of MRA and/or ACEi/ARB treatment at baseline. Provided the modelling assumptions are satisfied (e.g. sufficient numbers of responders / non-responders in each arm), these will be done by logistic regression.

If there is loss to follow-up, sensitivity analysis will be conducted. Given the binary nature of the primary outcome, extreme scenarios such as the worst case in the intervention group (all losses to follow-up classified as non-responders) and the best case in the control group (all losses to follow-up are responders) will be considered.

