#### Sample size estimation

Clinical evidence suggests that the proportion of patients reaching the target dose of RAASi in the control arm would be around 50% as a conservative estimation based on our experience. The study is powered to detect an effect size of the intervention of around 30%.

Group sample sizes of 52 will achieve approximately 90% power to detect a difference between the group proportions of 0.3 using a two-sided Z-test with pooled variance and a two-sided χ^2^ test. The proportion of responders in the placebo arm is assumed to be 0.5 with the corresponding proportion in the active arm 0.8 under the alternative hypothesis. The significance level (α) of the test is 0.05. This results in a total of 104 patients required and, accounting for 20% loss to follow-up, we will recruit 130 patients to be randomised to each group.

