## Discussion

This trial will be the first to look at the use of SZC for the maximisation of RAASi dosing in CKD patients. Our hypothesis is that SZC therapy will reduce the incidence of treatment-limiting hyperkalaemia in CKD-HF patients, allowing higher doses of RAASi therapy and therefore better clinical outcomes. Achievement of the participant’s target RAASi dose is the primary endpoint, and secondary endpoints include measures to assess safety in terms of hyperkalaemia, cardiovascular risk in terms of troponin T levels [19, 20], and efficacy in terms of time-to-target dose. We will also assess the impact of achieving target RAASi dosing on hospital admission rates and duration of stay, with the hope that optimum RAASi treatment will translate into reduced morbidity and improved QoL.

The strengths of the study include its randomised, double-blind design, and the favourable safety profile of the trial drug. We intend that the design will provide high-quality evidence that, if our hypothesis is supported, will help guide changes in clinical practise. As SZC is approved for the treatment of hyperkalaemia in the UK and has a favourable safety profile, our study has the benefit of being low-risk to participants.

The side-effect profile of SZC is minimal and hence we hope that adherence to the study protocol will be satisfactory. Our statistical predictions have nonetheless accounted for a 20% dropout rate owing to participants’ decisions, movements out of the area, death, progression to renal transplant, or other causes. Our study design focusses on a single recruitment centre.

The novel value of this study centres around (I) its examinations of SZC to limit hyperkalaemia and allow RAASi maximisation in the under-studied combined CKD-HF patient group, and (ii) its expansion of the currently limited safety data on the use of RAASi therapy in advanced CKD patients. The joint CKD-HF clinic approach is an emerging practise, and, if clinical benefit is proven, we would hope to investigate future studies with wider scope for more extensive population validity.

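### At the planned 20% loss, the one missing-data scenario the protocol names is a valid outer bound, but it can almost never confirm a real design-size benefit

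*Protocol article*

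**What the plan says.** Under Primary outcomes, the protocol article deems participants who leave before completion to be missing. The analysis section (Summary of baseline data and flow of patients) calls for an intention-to-treat chi-square test at 0.05. If there is loss to follow-up, it says sensitivity analysis will consider "extreme scenarios such as the worst case in the intervention group (all losses to follow-up classified as non-responders) and the best case in the control" arm, in which every loss counts as a responder. No milder or reverse scenario is named. The later section on missing or spurious data adds only a general undertaking to choose a suitable analysis.

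The sample size section gives the design values: "Group sample sizes of 52 will achieve approximately 90% power to detect a difference between the group proportions of 0.3", and "The proportion of responders in the placebo arm is assumed to be 0.5 with the corresponding proportion in the active arm 0.8". Recruitment is set "accounting for 20% loss to follow-up". The Discussion repeats that the calculation "accounted for a 20% dropout rate owing to participants’ decisions, movements out of the area, death, progression to renal transplant, or other causes".

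**The concern.** Because discontinuers drop out of the primary comparison, the sensitivity analysis is where a reader would look to judge whether dropout could explain the result. At 20% loss in both arms, the named scenario gives none of the lost SZC patients a response and all of the lost placebo patients one. The gap between this corner and the opposite corner (all lost SZC patients respond, no lost placebo patients do) is 40 points, wider than the 30-point effect the trial is built to detect.

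If the trial goes as designed, this one scenario would usually leave a positive result looking fragile. It would not show how extreme the missing outcomes have to be before the conclusion changes. The scenario also gives opposite outcomes to patients leaving two blinded arms, although the Discussion lists the causes of loss without distinguishing the arms.

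**Working it through.** **Inputs.**
- Response rates 0.5 (placebo) and 0.8 (SZC): "The proportion of responders in the placebo arm is assumed to be 0.5 with the corresponding proportion in the active arm 0.8".
- Test: "using a two-sided Z-test with pooled variance and a two-sided χ^2^ test"; "The significance level (α) of the test is 0.05".
- Loss: 20%.
- Size: 130 in total (Abstract) at 1:1 (Randomisation), so 65 per arm. The sample size section words it differently ("accounting for 20% loss to follow-up, we will recruit 130 patients to be randomised to each group"), so that reading is checked below as well.
- Assumptions not in the document: loss is equal in the two arms and unrelated to outcome; the number lost per arm is Binomial(65, 0.2) unless stated otherwise; the primary test is re-run on the scenario.

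**Step 1. The plan's own figure.** With mean rate 0.65,
n = [1.960 × √(2 × 0.65 × 0.35) + 1.282 × √(0.8 × 0.2 + 0.5 × 0.5)]² / 0.3² = 51.01, rounded up to 52 per arm. Power at 52 is 0.906. Inflation gives 104 / 0.8 = 130. The stated sample size reproduces.

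**Step 2. Expected rates in the scenario.** With loss L:
- SZC rate = (1 − L) × p_SZC
- Placebo rate = (1 − L) × p_placebo + L

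At L = 0.20:
- Design effect: 0.8 × 0.8 = 0.64 against 0.8 × 0.5 + 0.2 = 0.60. The 30-point difference becomes 4 points.
- No effect, both rates 0.5: 0.8 × 0.5 = 0.40 against 0.60, a 20-point deficit for SZC.

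**Step 3. Re-running the primary test.** Pooled Z (equivalent to chi-square without continuity correction), 65 per arm. Scenario probabilities agree between exact enumeration and simulation at 5%, 10% and 20% loss; the other entries are from simulation with 2 million trials.

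| Loss per arm | Completers power, 0.8 vs 0.5 | Scenario significant for SZC, 0.8 vs 0.5 | Significant completers results that lose significance | Scenario significant against SZC, 0.5 vs 0.5 |
|---|---|---|---|---|
| 5% | 95% | 82% | 14% | 7% |
| 10% | 94% | 54% | 43% | 19% |
| 15% | 92% | 24% | 74% | 38% |
| 20% | 91% | 7% | 92% | 61% |

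The fourth column counts only trials whose completers analysis was significant in favour of SZC. Over all trials at 20% loss, the scenario shows no significant benefit in 92.8%; that includes about 9% where the completers analysis was already non-significant.

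**Step 4. Other readings at 20% loss.** Each pair is the share of all trials without significant benefit under 0.8 vs 0.5, then the share with significant harm under 0.5 vs 0.5.
- Exactly 13 lost per arm: 96.3% and 61.8%.
- Continuity-corrected chi-square: 95.1% and 54.0%.
- 130 in each group, taken literally: 90.3% and 90.8%.
- Only the SZC half of the scenario applied: about 67% and 19%.
- Only the placebo half applied: about 34% and 19%.

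**Step 5. What a tipping-point grid would show.** Take a result close to plan: 42/52 on SZC, 26/52 on placebo, 13 lost per arm. For s lost SZC responders and c lost placebo responders, compare (42 + s)/65 with (26 + c)/65.
- s = 0: significant up to c = 4 (z = 2.12); lost at c = 5 (z = 1.94).
- s = 4: significant up to c = 9 (z = 1.99); lost at c = 10 (z = 1.82).
- s = 8 or more: significant for every c up to 13 (at s = 8, c = 13, z = 2.08).
- The named corner, s = 0 and c = 13, gives z = 0.54. On its own it reveals none of this.

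**The case against.** The case on the other side has real force.

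- The protocol speaks of scenarios in the plural, offers this one as an example and calls it extreme. It does not exclude milder ones, and a separate analysis plan may contain them. This stands: the scenario is the only one named, not the only one allowed.
- No threshold or pass/fail rule is attached to the sensitivity analysis. The percentages arise only if the chi-square test is re-run on the scenario. This stands as a stated assumption.
- A worst-case bound is sound. A result that survives it is robust to any pattern of missing outcomes, and failing it does not refute the primary result. This also stands.
- The 20% is an allowance used to inflate the sample size, and each participant is followed for only about two months. With 5% or 10% loss the problem is much smaller, as the table shows.

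A reader might infer that the scenario cannot tell a benefit from no effect. The figures do not support that: at 20% loss it shows significant harm in 0.8% of trials under the design effect and in 61% under no effect. A reader might also infer that it overturns a true benefit in 93% of trials, but that share counts trials in which there was no significant result to overturn.

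None of this removes the narrower point. The protocol does fix one concrete scenario, and its behaviour at the protocol's own loss and effect can be calculated.

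**Conclusion.** The concern holds in a limited form. If loss is near the planned 20% in each arm, the named scenario can almost never confirm a real 30-point benefit: about 92% of significant completers results lose significance, and with no effect at a rate of 0.5 about 61% of trials show significant harm. This rests on 65 per arm, equal loss unrelated to outcome, both halves of the scenario applied together, and re-use of the primary test at 0.05. At 10% loss the figures are about 43% and 19%; at 5%, about 14% and 7%.

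It does not follow that the scenario is invalid, that the protocol makes it a criterion for robustness, or that other sensitivity analyses are ruled out. The sample size and the primary test are unaffected, so severity is modest.

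**What to change.** In the analysis section, pre-specify a two-way tipping-point analysis for the primary outcome:

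- Let the number of responders among lost patients run from 0 to all, separately in each arm.
- For each combination, re-run the primary test and the 95% confidence interval for the difference.
- Report the boundary at which the conclusion changes, and discuss whether that boundary is plausible given the recorded reasons for loss.
- Keep the scenario already named as one corner of the grid, labelled as a bound.

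The cost is about one sentence in the plan and one small table or plot in the report, with no extra patients or data. The drawback is that the output is a boundary to be interpreted instead of a single result.

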#### Secondary outcome analysis

Descriptive summaries of the distribution of the secondary endpoints will be presented. More formal statistical analysis and modelling may also be performed: for responder/non-responder outcome (e.g. secondary outcomes 1 and 2), analysis may be done in the same manner as for the primary outcome. For time-to-event endpoints (e.g. secondary outcomes 3 and 4), survival techniques such as Kaplan-Meier estimates may be employed. The exact choice of analyses will be data-driven, so these analyses are to be regarded as explanatory.

#### Sample size estimation

Clinical evidence suggests that the proportion of patients reaching the target dose of RAASi in the control arm would be around 50% as a conservative estimation based on our experience. The study is powered to detect an effect size of the intervention of around 30%.

Group sample sizes of 52 will achieve approximately 90% power to detect a difference between the group proportions of 0.3 using a two-sided Z-test with pooled variance and a two-sided χ^2^ test. The proportion of responders in the placebo arm is assumed to be 0.5 with the corresponding proportion in the active arm 0.8 under the alternative hypothesis. The significance level (α) of the test is 0.05. This results in a total of 104 patients required and, accounting for 20% loss to follow-up, we will recruit 130 patients to be randomised to each group.

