**Methods:**

We propose a 1:1 randomised, double-blind, placebo-controlled trial in which participants will receive either SZC or placebo. We will up-titrate participants’ RAASi therapy while monitoring their serum potassium levels and adjusting their SZC dose if necessary. Participants with CKD and HF will be recruited from CKD and HF clinics at St George’s Hospital. The total study period will be 18 months; 130 participants will be enrolled for approximately two months each following screening. Our primary outcome will be the proportion of participants who achieve maximum RAASi dose while maintaining normokalaemia. Secondary outcomes include participants reaching maximum RAASi dose without severe hyperkalaemia; time from randomisation to hyperkalaemia; time from randomisation to severe hyperkalaemia; number of RAASi dose escalations per participant; final doses of RAASi therapy; changes in quality of life score, eGFR, ACR, serum sodium, troponin T; number and duration of hospital admissions; and within-participant change in serum potassium compared to baseline.

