## Background

Chronic kidney disease (CKD) is a common comorbidity in individuals with heart failure (HF), with a prevalence of 32% according to a 2013 meta-analysis of over one million individuals [1]. Patients with combined CKD-HF are at 2.3 times greater risk of all-cause mortality than those with HF alone [1]. Potentially life-saving medications for systolic HF are underused in combined CKD-HF due to risk of hyperkalaemia [2]. These medications include renin-angiotensin-aldosterone system inhibitors (RAASi): angiotensin converting enzyme inhibitors (ACEi), angiotensin receptor blockers (ARB), and mineralocorticoid receptor antagonists (MRA) [3, 4].

While numerous national and international guidelines recommend RAASi treatment in patients with combined CKF-HF [5–8], the risk of hyperkalaemia in CKD stage 4/5 patients is high and potentially fatal [9]. There is therefore reluctance amongst general practitioners, general physicians, and cardiologists managing these patients to prescribe medications that may increase serum potassium levels [10].

In a study of 1056 acute heart failure admissions in 851 patients at St George’s Hospital, London, patients with CKD stage 4/5 and systolic HF were less likely to receive ACEi or ARB compared to non-CKD patients (36% vs 84%, *p* < 0.001) and less likely to receive MRA (17% vs 57%, *p* < 0.001) [11]. These findings have led to the establishment of a joint kidney failure-heart failure service at St George’s Hospital, funded by three local clinical commissioning groups, to improve care for these patients. Audit of all new referrals to the kidney failure-heart failure clinic between March and September 2017 showed that only 3% of all patients with left ventricular systolic dysfunction were on maximum-dose ACEi/ARB, and only 2% were on maximum-dose MRA [12].

Recent studies have shown that sodium zirconium cyclosilicate (SZC) can lower serum potassium concentrations in non-CKD, CKD, and HF populations [13–16]. SZC is a zirconium silicate compound that acts as a selective potassium ion trap and is not absorbed from the gastrointestinal tract [17]. In a phase three randomised controlled trial of 258 patients with hyperkalaemia, SZC lowered serum potassium from 5.6 to 4.5 mmol/L in 48 h and maintained serum potassium of < 5.1 mmol/L in 90% of patients (compared with 48% of patients on placebo, *p* < 0.001) [15].

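### The sample-size paragraph randomises 130 patients to each group (260), but its own arithmetic and the abstract give 130 in total, 65 per group

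*Protocol article*

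**What the plan says.** Under Sample size estimation, the protocol article gives the design as "Group sample sizes of 52 will achieve approximately 90% power" for a difference of 0.3, "using a two-sided Z-test with pooled variance" and the equivalent chi-square test. It adds "The significance level (α) of the test is 0.05". The assumed rates are 0.5 on placebo and 0.8 on active treatment. The section then states a requirement of 104 patients overall, allows for 20% loss to follow-up, and concludes "we will recruit 130 patients to be randomised to each group".

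The Methods paragraph of the abstract says "130 participants will be enrolled for approximately two months each following screening". The Randomisation section fixes 1:1 allocation.

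On the control rate, the sample size section first says "the proportion of patients reaching the target dose of RAASi in the control arm would be around 50" per cent, on the basis of the investigators' experience. It then says "The proportion of responders in the placebo arm is assumed to be 0.5". Under Primary outcomes, a responder is someone who reaches the target RAASi dose and has no potassium value of 5.6 mmol/L or more after randomisation.

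**The concern.** The document carries two trial sizes that differ by a factor of two. The sample size paragraph is where a reader looks for the randomisation target, and its closing phrase disagrees with the calculation that leads to it. Anyone who takes that phrase at face value would plan for 260 patients at a single centre within 18 months. They would also place the first interim look, set at 10% of patients completing, at 26 patients instead of 13.

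The control rate raises a smaller question. The only rationale given for 50% concerns reaching the target dose. The tested outcome adds a potassium condition, in people who enter with potassium of 5.0–5.5 mmol/L. The responder rate cannot exceed the rate of reaching the dose. If 50% really is the dose rate, it is a ceiling for the placebo responder rate, and the text does not say why the two should be equal.

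**Working it through.** **Inputs, all from Sample size estimation unless noted.** Two-sided α = 0.05 (z = 1.960); power 0.90 (z = 1.282); placebo rate p₁ = 0.5; active rate p₂ = 0.8; pooled-variance Z-test; 20% loss; 1:1 allocation (Randomisation section).

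**Step 1: reproduce the group size.** With p̄ = (0.5 + 0.8)/2 = 0.65,

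n = [1.960·√(2·p̄·(1 − p̄)) + 1.282·√(p₁(1 − p₁) + p₂(1 − p₂))]² / (p₂ − p₁)²

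= [1.960·√0.455 + 1.282·√0.41]² / 0.09 = (1.322 + 0.821)² / 0.09 ≈ 51.0, just above 51, so 52 per group.

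Power at 52 is Φ[(0.3·√52 − 1.322)/0.640] = Φ(1.31) = 0.906. Exact enumeration of the uncorrected chi-square test gives 0.910. The stated 52 per group and approximately 90% both reproduce.

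**Step 2: reproduce the total.** 2 × 52 = 104, as stated.

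**Step 3: allow for loss.** 104/(1 − 0.2) = 130 over both groups, or 52/0.8 = 65 per group. This agrees with the abstract.

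**Step 4: test the sentence as worded.** 130 per group is 260 in total. After 20% loss, 104 per group remain. Power is Φ[(0.3·√104 − 1.322)/0.640] = Φ(2.71) = 0.997, which is not the stated 90%.

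**Step 5: look for another route to 130 per group.** A continuity correction gives 58 per group, a one-sided test 42, and unpooled variance 48. Inflating by multiplication gives 104 × 1.2 = 124.8, so 125 in total. None leads to 130 per group.

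**Step 6: sensitivity to the placebo rate.** The article gives no separate rate for the composite outcome, so the placebo rates below are assumptions. The difference is held at the stated 0.30, with 52 evaluable per group.

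| Placebo rate | Active rate | Power at 52 per group | n per group for 90% |
|---|---|---|---|
| 0.50 | 0.80 | 90.6% | 52 |
| 0.45 | 0.75 | 88.9% | 54 |
| 0.40 | 0.70 | 87.9% | 56 |
| 0.35 | 0.65 | 87.5% | 57 |
| 0.30 | 0.60 | 87.9% | 56 |
| 0.25 | 0.55 | 88.9% | 54 |
| 0.20 | 0.50 | 90.6% | 52 |

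If the stated active rate of 0.80 holds while the placebo rate is lower, power rises: 96.8% for 0.45 against 0.80, and 99.2% for 0.40 against 0.80.

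**The case against.** On the trial size, the best defence is that this is a slip of the pen. The intended total can be recovered from the 104, the 20% and the abstract, and nothing in the article plans recruitment or drug supply for 260. That is fair as to intent, and it keeps the remedy small. It does not make the sentence correct.

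On the control rate, a reader might infer more than the text supports.

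- **That the 90% power is for a dose-only endpoint.** It is not. The calculation assumes 0.5 for responders, the Primary outcomes section defines responders by dose and potassium together, and that status is what is tested. The gap lies in the rationale for the number, not in the endpoint that was powered.
- **That power collapses if the placebo rate is lower.** That requires holding the ratio 0.8/0.5 fixed so that the absolute gain shrinks. The article plans an absolute difference of 0.3 and states no ratio. Its hypothesis is that the binder reduces treatment-limiting hyperkalaemia, so a potassium condition could remove more placebo responders than active ones and widen the gap. The documents do not settle the direction.
- **That calling 50% conservative is wrong.** The word can mean a deliberately high placebo rate that leaves the active arm less room for gain. The text does not say which sense is meant.
- **That the audit in the Background, where "only 3% of all patients with left ventricular systolic dysfunction were on maximum-dose ACEi/ARB", contradicts 50%.** That figure describes new clinic referrals, not patients after protocol-driven up-titration, so it says nothing about the control rate in this trial.

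**Conclusion.** The phrase that assigns 130 patients to each group is wrong as written. The figure is the total for both arms, 65 per arm. The error is a factor of two (260 against 130), and it detaches the stated power (about 90%, reproduced at 90.6%) from the stated recruitment (about 99.7% after 20% loss). This rests only on the article's own inputs and needs no outside assumption. The rest of the calculation is sound.

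The control-rate point is minor. The 50% is carried from reaching target dose to the composite responder without a stated reason. With the stated 0.30 difference, the cost is at most about 3 percentage points of power for placebo rates from 20% to 50%, and those rates are assumed.

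**What to change.** Reword the end of the sample size paragraph to say that 130 patients will be recruited in total, with 65 allocated to each arm, so that it agrees with the calculation above it and with the abstract.

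In the same edit, state that 50% is the assumed placebo rate for the composite responder definition (target dose reached and no post-randomisation potassium of 5.6 mmol/L or more), and give the basis for it in one clause.

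Both are wording changes. Neither alters the design, the power statement or the number of patients.
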